## Abstract

**Background:**

Chronic kidney disease (CKD) is associated with a reduced quality of life and an increased risk of kidney failure, cardiovascular events, and all-cause mortality. Accumulation of nitrogen-based uremic toxins leads to worsening of symptoms in individuals with CKD. Many uremic toxins, such as indoxyl and p-cresol sulphate, are produced exclusively by the gut microbiome through the proteolytic digestion of aromatic amino acids. Strategies to reduce the production of these toxins by the gut microbiome in individuals with CKD may lessen symptom burden and delay the onset of dialysis. One such strategy is to change the overall metabolism of the gut microbiome so that less uremic toxins are produced. This can be accomplished by manipulating the energy source available to the microbiome. Fermentable carbohydrates which reach the gut microbiome, like resistant starch (RS), have been shown to inhibit or reduce bacterial amino acid metabolism. This study aims to investigate the effects of resistant potato starch (RPS) as a prebiotic in individuals with CKD before the onset of dialysis.

**Methods:**

This is a double-blind, randomized two-period crossover trial. Thirty-six eligible participants will consent to follow a 26-week study regimen. Participants will receive 2 sachets per day containing either 15 g of RPS (MSPrebiotic, resistant potato starch treatment) or 15 g cornstarch (Amioca TF, digestible starch control). Changes in blood uremic toxins will be investigated as the primary outcome. Secondary outcomes include the effect of RPS consumption on symptoms, quality of life and abundance, and diversity and functionality of the gut microbiome.

**Discussion:**

This randomized trial will provide further insight into whether the consumption of RPS as a prebiotic will reduce uremic toxins and symptoms in individuals who have CKD.

**Trial registration:**

ClinicalTrials.govNCT04961164. Registered on 14 July 2021

## Background

In Canada, the overall prevalence of chronic kidney disease (CKD) is ~ 13%, rising to ~ 30% in those over 65 [1]. CKD is associated with a reduced quality of life and an increased risk of kidney failure, cardiovascular events, and all-cause mortality [2–4]. An ageing population along with increasing rates of hypertension and diabetes mellitus are among the factors related to an increasing prevalence of end-stage kidney disease [5]. As kidney function declines, there is an accumulation of nitrogen-based uremic toxins which leads to worsening of symptoms and complications. Many uremic toxins, such as indoxyl and p-cresol sulphate, are produced exclusively by the gut microbiome [6] through the proteolytic digestion of aromatic amino acids (tyrosine and tryptophan, respectively) [7]. Strategies to reduce the concentration of these toxins present a low-risk, low-cost opportunity to lessen symptom burden in patients with CKD and may delay the onset of dialysis.

Indoxyl and p-cresol sulphate are thought to have negative effects on multiple organ systems and have been associated with reported clinical symptoms, such as uremic pruritus [8], and cardiovascular mortality in individuals with CKD [9–13]. Two approaches have been identified to deal with these toxins: binding or removing the toxins in the gut, or reducing their production [11]. Recent attempts to pharmacologically bind uremic toxins in the gut with activated charcoal have been unsuccessful in clinical trials [12], perhaps because the binding was not effective, or because the burden on participants (30 pills per day) was too much to maintain compliance. Strategies to reduce the production of these toxins by the gut microbiome in individuals with CKD may be more effective, especially if they have a lower patient burden [14]. One such strategy is to change the overall metabolism of the gut microbiome so that less uremic toxins are produced. This can be accomplished by manipulating the energy source available to the microbiome [7, 14]. Fermentable carbohydrates that reach the gut microbiome, like resistant starch, have been shown to inhibit or reduce bacterial amino acid metabolism [15, 16]. Raw potato starch (RPS), which is a R2-resistant starch, has been shown to increase carbohydrate-degrading bacteria, such as Bifidobacteria, and decrease bacteria with proteolytic activity, such as *Escherichia coli* [14, 17, 18]. RPS has also been shown to reduce the concentrations of gut microbiome-derived uremic toxins in pigs [19].

While animal and human studies involving resistant starch have shown the ability to change the gut microbiota and reduce the amount of uremic toxins, there are limited studies in individuals with CKD [14]. However, in one study conducted in individuals with CKD on dialysis, a reduction in uremic toxins following high-amylose cornstarch consumption for 6 weeks was observed [20]. High-amylose cornstarch is ~ 60% resistant starch by dry weight, whereas the RPS to be used in this proposal is ~ 70% resistant starch and ~ 10% other dietary fibres [17].

To our knowledge, no studies have investigated the effects of RPS as a prebiotic in individuals with CKD before the onset of dialysis.

## Methods/design

### Study design

The clinical trial is exploratory and will follow a 2-period double-blind cross-over design. The allocation ratio will be 1:1. It will take place at the Chronic Disease Innovation Centre (CDIC) at Seven Oaks General Hospital in Winnipeg, Canada. The study protocol flow chart is shown in Fig. 1. This trial will be conducted in compliance with Good Clinical Practice (GCP) and all local and national guidelines.

**Fig. 1 Fig1:**
[figure not shown]
Study protocol flow chart

Participants will consent to follow a 26-week study regimen. Each participant will receive 2 sachets per day containing either 15 g of RPS (MSPrebiotic, resistant potato starch treatment) or 15 g cornstarch (Amioca TF, digestible starch control). The powder in the sachets will be mixed in water and consumed, one sachet in the morning and one before bed. Participants will be instructed to consume the investigational product at least 2 h prior to or after taking any medication.

For the first 2 weeks, participants will go through a run-in period, where they will all receive the cornstarch control. During weeks 3 to 12 (period 1), participants will receive either RPS or cornstarch. The first treatment received will be determined by a randomization procedure. During weeks 13 to 16, participants will undergo a washout period where they will all consume cornstarch. During weeks 17 and 26 (period 2), participants will receive the treatment they did not previously consume (RPS or cornstarch, respectively).

Participants will complete questionnaires and food records at the beginning and end of each treatment period (Table 1). They will also provide blood, urine, and faecal samples for analysis (Table 1).

**Table 1 Tab1:** The schedule of enrolment, interventions, and assessments

Assessment	Screening and enrolment	Visit 1	Visit 2	Visit 3	Washout	Visit 4	Visit 5
Periods		Run-in		Period 1		Period 2	
Day in study		1	15	84	85–112	113	182
Informed consent	□						
Screening	□						
Demographics	□						
Medical history anthropometrics	□	□	□	□		□	□
Dietary recalls			□	□		□	□
SF-36, ESAS			□	□		□	□
Blood, urine, and stool collections			□	□		□	□
Adverse event			□	□		□	□

### Study participants

Thirty-six adults (18–85 years) with CKD will be recruited to the study via the advanced CKD clinic at Seven Oaks Hospital. [name] and [name] will oversee the recruitment.

#### Inclusion criteria

The participant may enter the trial if all of the following apply: the participant is willing and able to give informed consent for participation in the trial and has the ability to speak and read English; male or female, aged 18 years or above; females of child-bearing potential must agree to use a medically approved method of birth control for the duration of the study; all hormonal birth control must have been in use for a minimum of 3 months; acceptable methods of birth control include hormonal contraceptives including oral contraceptives, hormone birth control patch, vaginal contraceptive ring, injectable contraceptives, hormone implant, double-barrier method, intrauterine devices, and non-heterosexual lifestyle or agrees to use contraception if planning on changing to heterosexual partner(s) and vasectomy of partner at least 6 months prior to screening; the estimated glomerular filtration rate (eGFR) is < 15 mL/min/1.73 m^2^ for the past 3 months; and in the investigator’s opinion, participants are able and willing to comply with all the trial requirements.

#### Exclusion criteria

The participant may not enter the trial if any of the following apply: the participant is cognitively impaired and cannot give consent or participate in the group programme; the participant has an existing relationship with the research team, such as supervisory relationship (student, employee) or familial relationship (child, spouse, etc.); participants who indicate that they cannot consume study treatments; participants who indicate they are allergic to potatoes or corn; female participants who are pregnant, lactating, or planning pregnancy during the trial; history of renal transplant, ongoing dialysis, use of antibiotics (last 3 months), bowel diseases, cancer, surgically removed bowel, or any gastrointestinal surgery (e.g. intestinal resection, gastric bypass, colorectal surgery); inability to consume treatment due to swallowing or GI issues; participating in another interventional trial that could influence the intervention or outcome of this trial; participants with uncontrolled diabetes with A1C > 10%; participants who consume probiotic supplements; participants with abnormal constrictions of the gastrointestinal tract, diseases of the oesophagus, and/or the superior opening of the stomach (cardia), potential or existing intestinal blockage, paralysis of the intestine, megacolon, faecal impaction, appendicitis, a sudden change in bowel habits that has persisted for more than 2 weeks, undiagnosed rectal bleeding, or failure to defaecate following the use of another laxative product; participants with severe anaemia (haemoglobin less than 70); participants taking medications which inhibit peristaltic movement (e.g. opioids, loperamide); and participants able to maintain high fibre/adequate fibre intake through diet or taking other fibre supplements.

#### Recruitment

A research coordinator will work with someone within the circle of care (such as a nurse, a clinical clerk, or a physician) of patients attending the Manitoba renal programmes interdisciplinary CKD clinic at Seven Oaks Hospital to pre-identify potentially eligible participants.

The first point of contact will occur during routine clinical care or through virtual meetings. An individual in the patient’s circle of care will inform the patient that they may be eligible to participate in a research study and ask for their permission for the research coordinator to contact them to discuss the study in detail that day or at a later time, through a virtual or in-person visit. This is meant to be a brief conversation, and the main purpose is to seek permission for the individual to be contacted by the research coordinator and to do this via someone in the patient’s circle of care. We will ensure that all clinical conversations (e.g. patient’s health, updates, appointment reminders) will be completed first before the study is introduced to them.

The second point of contact will be made by the research coordinator through virtual meetings or in-person visits to explain the study in greater detail to the patient. Patients that are interested in the study will be given a letter of information and consent form to review and sign through the Research Electronic Data Capture (REDCap) platform or in paper form. A participant ID log will be kept recording the patients who enrol into the study. It is expected that the recruitment of the 36 participants will occur over a 3-month period.

### Treatments

The treatments will consist of (1) 30 g of RPS (MSPrebiotic) or (2) 30 g digestible cornstarch (Amioca TF) per day. Digestible cornstarch was chosen as the comparator because it is visually similar to the RPS but contains no resistant starch. These treatments will be given to participants in 2 sachets per day, which are to be mixed with water and consumed, one in the morning and one in the evening before bed. The dosage of 30 g is based on a previous study of RPS in older adults [17]. The resistant potato starch and cornstarch will be pre-packed in labelled packages provided by the manufacturer. The cornstarch and resistant potato starch sachets will be stored at room temperature until it is dispensed to participants. Courier will be available as an option to deliver the packages to the study participants.

### Compliance

Diaries with daily checklists for the 2 sachets will be given to the participants for each day during the run-in, washout, and treatment periods. These will be used to monitor their compliance with the study protocol. Additionally, participants will be instructed to return all empty sachets for counting purposes. Compliance for both groups will be defined as an attendance of ≥ 90% of the scheduled visits with the research team and ≥ 80% of the required treatments consumed according to diary entries and returned sachets. Participants will be monitored every week by the research team through phone calls or online videos. Additionally, there will be a study dispensing log which will be used to track all study treatments given to each of the participants. This log will include participant ID, date of dispensing, randomization code, and the returned sachet counts. Concomitant medication will be recorded at the end of the run-in and each treatment period.

### Assessments

#### Baseline assessments

After screening, eligible participants will receive cornstarch sachets for the first 2 weeks during a run-in phase; however, they will be instructed that they could be receiving cornstarch or resistant potato starch. Besides cornstarch sachets, participants will also receive the Medical Outcomes Study Short Form 36-item (SF-36) and Edmonton Symptom Assessment Scale (ESAS) questionnaires, the link to an Automated Self-Administered 24-h Canada (ASA24) dietary recall survey, a tape measure, a weight scale, and faecal sample collection kits.

At the end of the second week of the run-in period, study coordinators will book a virtual/in-person meeting with participants to instruct and measure body weight and waist circumference, go through medication/supplement condition, and give a general instruction on how to fill in SF-36, ESAS, and ASA24 questionnaires. Study coordinators will also give a brief introduction about blood, urine, and faecal collection steps and then send a lab requisition to the participants.

#### Ongoing assessments

Participants will be able to contact the study team at any time and will be given options to do so (text, voice call, video link, urgent in-person appointment). After enrolment in the study, participants will have follow-up virtual/in-person study visits as described in Table 1. Study visits will be acceptable on days within ± 5 days.

### Outcome measures

Serum concentrations of indoxyl and p-cresol sulphate are considered the primary outcome of this trial. This is to investigate how RPS consumption influences blood uremic toxins. The abundance, diversity, and functionality of the gut microbiome will be investigated as the secondary outcomes. Samples will be sent out for blood, faecal, and urine metabolomics analysis and gut microbiome analysis, following shipping guidelines of the contracted service providers, University of Manitoba policies, and all applicable local and national regulations.

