#### Uremic toxin measurement

Serum samples of indoxyl and p-cresol sulphate will be collected by the start and end of each treatment period. The concentrations of free and total p-cresol sulphate and indoxyl sulphate will be measured by high-pressure liquid chromatography [21]. Total p-cresol sulphate and indoxyl sulphate will be measured after deproteinization of serum with ethanol. These analyses will be conducted at McMaster University in Hamilton, ON.

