
Effects of treatment on linear outcomes at the end of each period will be analysed by the SAS MIXED (SAS 9.4) procedure. Sequence and sex will be included in the model as fixed factors, and participants will be included as a repeated factor. The normality of the data distribution will be done using the Shapiro-Wilk test, and the non-normal variables will be transformed prior to analysis. Demographic data will be reported as the mean ± standard deviation. The results will be reported as least-squared means ± standard error of the mean (SEM) unless otherwise specified. Statistical significance will be set at *p* < 0.05 for all analyses. The Data Science Platform in CHI will provide data management support in addition to biostatistics support for the project.

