### Sample size calculation

A final samples size of 30 participants in this study will be able to detect a difference between the treatments in total p-cresol sulphate of 17.5 μmol/L, or ~ 15% change, at a power of .88 (alpha = 0.05, two-sided), given a within-person correlation of .79 [23] and an estimated standard deviation of 45 μmol/L [9] for total p-cresol sulphate. A 30% or greater drop in uremic solutes would be considered clinically significant, warranting additional trials investigating this prebiotic intervention in CKD, and we are confident we would be able to detect such a change should it occur. To account for the loss of power due to dropouts, we will recruit 36 participants.

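### The primary outcome is two toxins with no primary fraction and no success rule, while only total p-cresol sulphate is powered; a claim on either toxin would carry about 7–10% false-positive risk

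*Protocol article*

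**What the plan says.** Four places in the protocol article bear on this.

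- **Outcome measures:** "Serum concentrations of indoxyl and p-cresol sulphate are considered the primary outcome of this trial". Two analytes are presented as one outcome, with no fraction named.
- **Uremic toxin measurement:** "The concentrations of free and total p-cresol sulphate and indoxyl sulphate will be measured by high-pressure liquid chromatography". This describes the assay and does not say which fraction is primary.
- **Statistical analysis:** "Statistical significance will be set at *p* < 0.05 for all analyses". The only multiplicity steps in that section are a Tukey adjustment and a q-value threshold of 0.1, both within the microbiome analysis. Neither covers the serum toxins.
- **Sample size calculation:** 30 final participants "will be able to detect a difference between the treatments in total p-cresol sulphate". No effect size, standard deviation or power is given for indoxyl sulphate or for any free fraction.

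The article gives no testing order, no split of alpha, and no rule on whether one toxin or both must succeed. The Study design section calls the trial exploratory.

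**The concern.** The sample size section treats the primary question as one test of one measure at two-sided 0.05. The outcome section poses it for two toxins and leaves the fraction open. The general threshold lets each test be read at 0.05. Followed as written, nothing stops the primary outcome from being called positive on whichever toxin falls below 0.05.

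The consequence is limited but real. The false-positive chance for an either-toxin claim is above the level used to plan the trial, and the claim could rest on indoxyl sulphate, for which no power is stated. A reader of the results could not tell from this document which result was meant to decide the primary question.

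**Working it through.** **1. Reproduce the stated power.** The Sample size calculation section gives n = 30, a difference of 17.5 μmol/L, "an estimated standard deviation of 45 μmol/L", a within-person correlation of 0.79, two-sided alpha 0.05 and power 0.88.

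- SD of the within-person difference = 45 × √(2 × (1 − 0.79)) = 45 × √0.42 = 29.16 μmol/L
- Standard error = 29.16 / √30 = 5.32 μmol/L
- Noncentrality = 17.5 / 5.32 = 3.29
- Two-sided paired t-test power: 0.888 with 29 degrees of freedom, 0.887 with 28

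This agrees with the stated 0.88. The calculation is sound for the one measure that it covers.

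**2. False-positive chance if either toxin counts.** There are two tests, each at 0.05, with no effect on either toxin.

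- Independent tests: 1 − 0.95² = 0.0975
- Correlated tests, by simulating two equicorrelated normal statistics (1,000,000 draws):

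| Assumed correlation | Chance of at least one p < 0.05 |
|---|---|
| 0 | 9.75% (exact) |
| 0.5 | 9.1% |
| 0.8 | 7.8% |
| 0.9 | 7.0% |
| 0.95 | 6.4% |

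The article gives no correlation between the toxins, so these values are assumptions. If the fraction were also chosen after the results were seen, the chance would rise further. No figure is given for that case because the article does not define such a family of tests.

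**3. If both toxins must succeed.** The false-positive chance stays at or below 5%. If indoxyl sulphate had the same power and the tests were independent (both assumptions), joint power would be 0.888² = 0.79.

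**4. What each repair does to the power for total p-cresol sulphate.**

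| Rule | Alpha for total p-cresol sulphate | Power, 30 completers | Power, 36 completers | Completers for 0.88 |
|---|---|---|---|---|
| Tested first in fixed sequence | 0.05 | 0.888 | 0.938 | 30 |
| Bonferroni over two toxins | 0.025 | 0.816 | 0.890 | 35 |

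The fixed sequence holds the error over the two toxins at 5% and leaves the planned power and sample size unchanged.

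**The case against.** **The 5% is not wrong for the test it describes.** This stands. The alpha in the sample size section belongs to the single test of total p-cresol sulphate and holds for it. The article never claims 5% across the toxins. A reader might infer that the stated error rate is false, but the defect is a missing decision rule.

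**The article does not make four measures primary.** This also stands. A reader might count free and total of each toxin as four primary tests, but the assay paragraph only says what will be measured. Free toxin is also a component of total toxin, so treating all four tests as independent would overstate the problem. The firm count is two.

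**The analysis plan may settle this.** Partly right. Testing order is often left to an analysis plan, and adjusted p-values could be compared with 0.05 without contradicting the general threshold. The q-value threshold of 0.1 in the same section suggests that the 0.05 rule is a default. Even so, the mismatch lies within this document: two toxins in the outcome section, one fraction of one toxin in the sample size, and a single threshold for everything.

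**A chance finding would not launch the larger trial.** A reader might infer that significance on an unpowered measure would justify it. The sample size section instead ties further trials to a drop of at least 30%. For total p-cresol sulphate the implied mean is 17.5 / 0.15 = 117 μmol/L, so 30% is about 35 μmol/L. That is 35 / 5.32 = 6.6 standard errors, so a chance crossing is negligible. The article gives no SD for the other measures, so the same check cannot be made for them.

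**The trial is exploratory.** This lowers the stakes, and strict error control over two related biomarkers is partly a matter of judgement. But the article still names a primary outcome, plans its size on alpha 0.05 and sets a significance threshold, so the rule for reading the primary outcome should be clear.

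**Conclusion.** The concern holds as a gap in the primary decision rule. Two toxins are primary, the fraction is unnamed, one threshold applies throughout, and only total p-cresol sulphate is powered. If success on either toxin counts, the false-positive chance is about 7–10%, assuming a correlation between the two tests of 0.9 down to 0. It remains above 5% even at 0.95. The result depends on the either-toxin reading, which the article permits but does not state. A both-required reading would keep 5% at some cost in power, and the article does not state that either. The sample size arithmetic needs no correction. The point is worth acting on because the repair is cheap, not because the trial's conclusions are in danger.

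**What to change.** In Outcome measures, name the end-of-period total fraction as primary for both toxins and state a fixed order. Total p-cresol sulphate is tested first at two-sided 0.05. Total indoxyl sulphate is tested at two-sided 0.05 only if the first test succeeds. Report free fractions and all other outcomes as secondary, with estimates and confidence intervals. Reword the general threshold in Statistical analysis to match.

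This keeps power at about 0.88 with 30 completers, leaves recruitment at 36, and keeps both toxins in the primary family. Requiring both toxins, or Bonferroni over two, would also control the error, but with the lower power shown above.

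There are two costs. The trial is registered, so this is a documented amendment. It should be dated before unblinding, which is feasible because the article keeps treatments blinded until the analyses are complete, apart from adverse-event unblinding and the independent nephrologist's midpoint safety review. And indoxyl sulphate can be claimed only after p-cresol sulphate succeeds.
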